### Cost-effectiveness analysis (CEA)

A cost-effectiveness analysis, comparing 4 less intensive screening strategies with IADPSG criteria will be conducted on an intention-to-treat basis by estimating various parameters including Quality-adjusted life years (QALYs), incremental cost-effectiveness ratio (ICER), and incremental net benefit (INB). To estimate mean cost in each treatment group, regression models will be used. General linear models (GLM) with appropriate variance functions e.g. gamma, Poisson, etc. and link will be used to identify the relationship between treatment allocation and costs after adjusting for minimization and the appropriate prognostic covariates at baseline (e.g. Baseline EQ-5D score). To estimate the incremental effect of the treatment indicator variable, recycled predictions will be used [64].

A sensitivity analysis will be conducted to assess how sensitive the cost-effectiveness results are to variation in key parameters including cost.

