**Methods:**

This study is a randomized community non-inferiority trial among 30,000 pregnant women in five different geographic regions of Iran, who were randomly assigned to one of the five GDM screening methods. All first trimester pregnant women, seeking prenatal care in governmental health care systems, who met our eligibility criteria were enrolled. The criteria suggested by the International-Association-of-Diabetes-in-Pregnancy-Study-Group, the most intensive approach, were used as reference. We used the non-inferiority approach to compare less intensive strategies to the reference one. Along with routine prenatal standard care, all participants were scheduled to have two phases of GDM screening in first and second-trimester of pregnancy, based on five different pre-specified protocols. The screening protocol included fasting plasma glucose in the first trimester and either a one step or a two-step screening method in the second trimester of pregnancy. Pregnant women were classified in three groups based on the results: diagnosed with preexisting pre-gestational overt diabetes; gestational diabetes and non-GDM women. Each group received packages for standard-care and all participants were followed till delivery; pregnancy outcomes, quality of life and cost of health care were recorded in detail using specific standardized questionnaires. Primary outcomes were defined as % birth-weight > 90th percentile and primary cesarean section. In addition, we assessed the direct health care direct and indirect costs.

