There is lack of ideal and comprehensive economic evaluations of various GDM strategies; the majority of existing cost-effective analyses are based on decision analysis modelling not real data, limited obtained from randomized clinical trials that documented controversial results [20, 30–38]. In addition most studies have been conducted in well-developed high-income countries which obviously have more developed healthcare systems than low and middle-income countries, where gestational diabetes has the highest prevalence. According to a WHO report, global and local decision-making regarding GDM strategies are challenging due to the lack of optimum economic evaluations of various GDM screening protocols, making it difficult to validated implement any national recommendations from a health economic perspective [31]. Since resources are unavoidably scarce, national health care interventions should be assessed for their impact on costs as well as on clinical outcomes; the most highly recommended practice is that economic evaluation should be an integral part of randomized clinical trials [39]; each population needs to adopt its community specific guidelines [40].

In this ongoing randomized community-field non-inferiority trial, we aimed to compare the cost-effectiveness of five different pre-defined GDM screening protocols, both one and two step, using different fasting plasma glucose thresholds to ascertain the optimum GDM screening protocol.

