### Sample size calculation

Based on previous studies, we assumed that the primary event rate of macrosomia to be equal to 10% for all groups with no difference. To obtain a statistical power of 85% with a 1-sided type one error of 0.005 (considering multiple comparisons) approximately 4700 patients per group are needed to show the non-inferiority of more intensive compared to lower intensive strategies with a marginal difference of 0.03. With a design effect of 0.001 (for cluster sampling) and loss to follow-up of 11%, sample size reached to 5200 in each group [42].

In addition, superiority analyses will be designed to show that one screening strategy is superior to another after non-inferiority has been demonstrated.

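### The cost-effectiveness analysis is framed as four contrasts with the IADPSG reference, although the aim is to find the best of five mutually exclusive strategies

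*Protocol article*

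**What the plan says.** The last paragraph of the Background gives the purpose of comparing the five protocols: "to ascertain the optimum GDM screening protocol". Under Overall study design and Randomization and allocation, each city is assigned one protocol, so the five are mutually exclusive options for a policy maker.

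The Methods part of the abstract describes the IADPSG criteria as "the most intensive approach, were used as reference". By the thresholds in Table 1 this is protocol A.

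The section Cost-effectiveness analysis (CEA) then fixes the comparison: "A cost-effectiveness analysis, comparing 4 less intensive screening strategies with IADPSG criteria will be conducted on an intention-to-treat basis". The same sentence lists QALYs and "incremental cost-effectiveness ratio (ICER), and incremental net benefit (INB") as quantities to be estimated. The section adds: "To estimate mean cost in each treatment group, regression models will be used". It names no comparison among the four less intensive strategies and does not say which measure decides.

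The section Bayesian and Markov Modeling adds Bayesian modelling of costs and benefits, a Markov model, and a decision tree with a probabilistic step. It states no comparators for any of them.

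**The concern.** The aim is a choice among five options, but the comparison set holds four pairs that all contain A.

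An ICER answers whether moving from one strategy to another is worth it. With several exclusive options, the relevant move is to the next non-dominated strategy on the cost-effect frontier, not always to the same reference. Less intensive strategies may well save money at a small health loss. An acceptable ICER there is a large saving per QALY lost, and several strategies can pass against A at once. One of those passing may cost more and do less than another, and nothing in the ICERs against A shows it.

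Some of the questions built into Table 1 are also contrasts without A. B and C differ only in whether two abnormal values or one define GDM, whereas A and B differ in that rule and in the first-trimester threshold. C and E compare the one-step and two-step methods at the higher first-trimester threshold. D and E isolate that threshold within the two-step method. Four contrasts with A give no interval for any of these.

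At stake is the policy recommendation. It could rest on a strategy that another one beats, or name a best strategy without saying how certain that is.

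**Working it through.** **Inputs.** The article states no cost, QALY or willingness-to-pay figure, so there is no figure of the plan to reproduce. All costs, QALYs and thresholds below are assumed. Only the comparison set (four strategies, each against A) and the measures (ICER, INB) come from the article.

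**Step 1: does INB against A rank all five?** With threshold λ, mean QALY Q and mean cost C:

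INB_k = λ(Q_k − Q_A) − (C_k − C_A) = (λQ_k − C_k) − (λQ_A − C_A) = NMB_k − NMB_A.

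The reference term is the same for every k, and INB_A = 0. The order of the INBs is therefore the order of the net monetary benefits (NMB) of all five strategies. This is algebra and holds at any fixed λ.

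**Step 2: do ICERs against A rank them?** Take two strategies and λ = 20,000 per QALY.

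- C against A saves 40 and loses 0.001 QALY: 40 / 0.001 = 40,000 saved per QALY lost.
- E against A saves 50 and loses 0.002 QALY: 50 / 0.002 = 25,000.
- Both exceed 20,000, so both pass, and E is the cheaper.
- E against C saves a further 10 for a further 0.001 QALY: 10 / 0.001 = 10,000, which fails.
- INB against A: C = 20,000 × (−0.001) + 40 = 20; E = 20,000 × (−0.002) + 50 = 10.

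Choosing E forgoes half of the available gain.

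**Step 3: five strategies, λ = 20,000.**

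| Strategy | Cost | QALY | Saved per QALY lost, against A | INB against A |
|---|---|---|---|---|
| A | 1000 | 0.700 | – | 0 |
| B | 700 | 0.690 | 300 / 0.010 = 30,000 | 300 − 200 = 100 |
| C | 850 | 0.697 | 150 / 0.003 = 50,000 | 150 − 60 = 90 |
| D | 880 | 0.695 | 120 / 0.005 = 24,000 | 120 − 100 = 20 |
| E | 600 | 0.684 | 400 / 0.016 = 25,000 | 400 − 320 = 80 |

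All four pass against A. D is among them, although C is cheaper and more effective than D. The most favourable ICER picks C, but the highest net benefit is B.

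The frontier gives the right answer. Remove D and order by cost: E to B costs 100 / 0.006 = 16,667 per QALY gained, B to C costs 150 / 0.007 = 21,429, and C to A costs 150 / 0.003 = 50,000. At 20,000 one moves from E to B and stops there, in agreement with INB.

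**Step 4: is this one contrived example?** In 200,000 random sets, A cost 1000 with 0.700 QALY, the other four saved 0 to 500 and lost 0 to 0.02 QALY (both uniform), and λ was 30,000.

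- The highest INB against A was the true optimum in 100% of sets, as Step 1 requires.
- The most favourable ICER against A, or A if none passed, was the wrong choice in 11.4%.
- More than one strategy passed against A in 55.2%.
- At least one passing strategy was dominated in 25.6%.

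The last three percentages depend on the assumed ranges.

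**Step 5: uncertainty.** For two alternatives, say C and E, Var(INB_C − INB_E) = Var(INB_C) + Var(INB_E) − 2 Cov(INB_C, INB_E). Both INBs contain the same estimate for A, so the covariance is not zero in general. Separate intervals against A do not show it. The interval for C against E, and the probability that each of the five has the highest net benefit, need the joint distribution over all arms.

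**The case against.** The strongest reply is that the plan already names the right measure. INB stands in the same sentence as the ICER, and by Step 1 it ranks all five strategies correctly at any fixed threshold. A wrong choice in Steps 2 and 3 arises only if INB is ignored, and the article states no rule of adopting the cheapest strategy whose ICER passes. This part stands in full. A reader might infer that the plan offers nothing but ICERs against A, or that it cannot identify the best strategy. The documents support neither.

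The second reply is that mean costs by arm, Bayesian modelling and a probabilistic decision tree could deliver any contrast among B to E. This stands as to capability: nothing further need be collected. It does not show that those contrasts are planned, since the only comparison set stated for the economic analysis contains A in every pair. The superiority analyses under Sample size calculation foresee one strategy against another but are not tied to costs or QALYs.

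The third reply is that a condensed article may leave sequential ICERs, the threshold range and the probability of being best to a full plan. Their absence alone would be no finding. The point here is what the article does state: a comparator set that does not match its aim.

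A reader might also infer that the ICER denominator is centred on zero, because the sample size section takes the event rate as "equal to 10% for all groups with no difference". That assumption concerns macrosomia, whereas effectiveness here is QALYs from the EQ-5D. It says nothing about the QALY difference. Nor does the article plan pairwise probabilities of being cost-effective against A, so it cannot be faulted for them.

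**Conclusion.** The concern holds in a limited form. The stated comparison set does not fit the stated aim. INB point estimates against A suffice for ranking. ICERs against A do not, and can make a dominated strategy look acceptable. Contrasts with A alone leave out the uncertainty of comparisons among B to E and the probability that each strategy is best.

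The equivalence of INB and net-benefit ranking is algebraic. So is the existence of the ICER failure, which one counterexample proves. Its frequency in this trial is unknown: 11.4% wrong choices and 25.6% of sets with a dominated strategy passing describe the assumed ranges only. The practical risk depends on whether the recommendation will rest on ICERs or on INB, which the article does not say. The change should be made before the economic analysis is run. It does not put the trial's data in question.

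**What to change.** Amend the section Cost-effectiveness analysis (CEA) along these lines:

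- All five strategies are compared simultaneously.
- The recommendation rests on the net benefit of each strategy over a stated range of willingness-to-pay thresholds, with intervals for the between-strategy differences of interest, including those among B to E.
- The probability that each strategy has the highest net benefit is reported at each threshold, taken from the joint distribution so that the five sum to one.
- Strategies are ordered by mean cost, dominated and extendedly dominated ones are removed, and ICERs are given only between successive strategies on the frontier.
- Contrasts with the IADPSG reference remain as supporting information.

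State that the probabilistic decision tree uses the same five-way comparison. The cost is a change of wording and some extra tables; the data and the models stay the same.

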## Materials and methods

### Research questions and objectives

This study is being performed to provide real data collected from an unbiased population trial for assessment of the following hypothesis: (i) the prevalence of GDM when using the less intensive GDM screening strategies is not more than obtained using the IADPSG criteria. (ii) The pre-specified primary outcomes in less intensive GDM screening strategies are not worse than those obtained using IADPSG criteria. (iv) The cost of health care using less intensive GDM screening strategies is not higher than incurred using IADPSG criteria. (v) The numbers needed to treat (NNT) to prevent one primary outcome in less intensive strategies are the same as those obtained using IADPSG criteria.

The cost of prevention for one primary outcome in less intensive strategies is the same as that for IADPSG criteria.

According to our research hypothesis, primary outcomes hence are: percentage of birth weight > 90th percentile and primary cesarean section. Secondary outcomes are prevalence of neonatal hypoglycemia, birth weight < 10th percentile, neonatal admission to the intensive care unit, shoulder dystocia and birth trauma including fracture of clavicle and brachial plexus injury, intrauterine fetal death, preeclampsia and preterm labor, neonatal hyperbilirubinemia and hypocalcemia. In addition, the study will assess the direct health care costs including prenatal clinic visits, obstetrician visits, endocrinologist visits, dietician visits, blood glucose monitoring equipment, laboratory test cost, pharmacotherapy, additional fetal well-being assessments and hospitalization as well as indirect cost of productivity loss and charges to the family including traveling, food substitution, mother time off paid work, and partner time off work.

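### The hypotheses of equal NNT and equal cost per primary outcome prevented divide by a difference that the trial plans as zero, so they are not reliably testable as worded

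*Protocol article*

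**What the plan says.** The protocol article, under Research questions and objectives, lists its hypotheses. Hypothesis (v) is that the NNT to prevent one primary outcome is equal under the less intensive strategies and under IADPSG. An unnumbered hypothesis follows: "The cost of prevention for one primary outcome in less intensive strategies is the same as that for IADPSG criteria". Hypothesis (iv), by contrast, is a plain comparison of cost: not higher than under IADPSG. The primary outcomes are birth weight above the 90th percentile and primary cesarean section.

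Under Sample size calculation the trial is sized on "the primary event rate of macrosomia to be equal to 10% for all groups with no difference", with a non-inferiority comparison "with a marginal difference of 0.03". Superiority analyses are to follow once non-inferiority is shown.

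Table 1 defines five protocols, A to E. All of them screen in both the first and the second trimester.

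Under Cost-effectiveness analysis (CEA), the four less intensive strategies are compared with IADPSG by "estimating various parameters including Quality-adjusted life years (QALYs), incremental cost-effectiveness ratio (ICER), and incremental net benefit (INB". The Questionnaires section states that effectiveness is measured in QALYs from the EQ-5D 3L.

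**The concern.** An NNT is one divided by a risk difference. A cost per outcome prevented is a cost divided by a number of outcomes prevented, which is also a risk difference. A statement that such a quantity is equal for two strategies needs a finite value for each strategy, and so a reference against which outcomes are prevented. An unscreened or untreated arm would supply one, but the trial has none. What randomisation does supply is each less intensive strategy against IADPSG, and the trial is planned on that difference being zero for macrosomia. At zero both ratios have no finite value, and near zero their sign is decided by chance.

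The article offers its results to policy makers. If the strategies turn out as alike as planned, cost-per-case and NNT figures would be mostly noise, and two stated hypotheses would have no usable answer. Even with a stable ratio, equality without a margin cannot be confirmed: failing to find a difference does not show sameness.

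**Working it through.** **Inputs (Sample size calculation).** Macrosomia 10% in every group, true difference 0; margin 0.03; one-sided alpha 0.005; power 85%; about 4,700 per group before loss; 11% loss; 5,200 per group enrolled.

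**The plan's own figure.** n = 2 × 0.1 × 0.9 × (2.576 + 1.036)² / 0.03² = 2,610 per group, so the stated 4,700 does not reproduce from these inputs. The loss step does, roughly: 4,700 / 0.89 = 5,281 and 4,700 × 1.11 = 5,217, against 5,200. The argument does not depend on how 4,700 arose. I take it as the evaluable number.

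**Precision of the denominator, no clustering.** SE = sqrt(2 × 0.1 × 0.9 / 4,700) = 0.0062. The 95% half-width is 1.96 × 0.0062 = 0.0121, or 1.21 points. An estimate of exactly zero gives an NNT interval from 1 / 0.0121 = 82 through infinity to −82. With 5,200 per group the SE is 0.0059, so the choice between the two numbers matters little.

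**How often the ratio has no bounded interval.** The 95% Fieller set for 1/ΔE or ΔC/ΔE (ΔE the effect difference, ΔC the cost difference) is unbounded whenever |estimated ΔE| < 1.96 SE. For a true difference δ this has probability Φ(1.96 − δ/SE) − Φ(−1.96 − δ/SE).

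| True difference | δ/SE | Unbounded, no clustering | Unbounded, variance doubled |
|---|---|---|---|
| 0 | 0 | 95% | 95% |
| 0.5 points | 0.81 | 87% | 91% |
| 1 point | 1.62 | 63% | 79% |
| 2 points | 3.23 | 10% | 37% |
| 3 points | 4.85 | 0.2% | 7% |

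The δ/SE column is for no clustering. The last column uses SE = sqrt(2) × 0.0062 = 0.0088.

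The doubling is an assumption. The article allocates protocols to 25 cities, so 5 per protocol and about 4,700 / 5 = 940 women per city if sizes were equal. It states a design effect of 0.001, which cannot be one. If 0.001 is read as an intracluster correlation, the design effect is 1 + 939 × 0.001 = 1.94. Inflation of 5 or 10 (also assumed) would widen the half-width to 2.7 or 3.8 points.

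**Net benefit by comparison.** INB = λ × ΔE − ΔC, with λ the value placed on one unit of effect. At ΔE = 0 it equals −ΔC. It stays finite and has an ordinary interval at every row of the table.

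**The case against.** There are four arguments on the other side.

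- **Assuming equality is only a sizing convention.** It is the usual way to size a non-inferiority trial and is not a forecast, and superiority analyses are planned. This stands. A reader might infer that the hypotheses cannot be tested at all, but the table does not support that: at true differences of 2 to 3 points the ratio against IADPSG is mostly estimable without clustering. Power for superiority at one-sided 0.005 with 4,700 per group and no clustering is 18% at 1 point, 79% at 2 and over 99% at 3.

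- **The economic analysis is not merely a ratio.** This also stands. A reader might infer that the planned ICER has a zero denominator too. The documents do not support that: the no-difference assumption concerns macrosomia, the economic effect is the QALY, and no QALY difference or standard deviation is given from which to compute anything. Net benefit stands beside the ICER, and hypothesis (iv) is a cost difference.

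- **The hypothesis may compare two strategy-specific costs of prevention.** On that reading each strategy is set against some common reference, and there is no incremental ratio between strategies. But such a reference is not randomised here. Decision-tree and Markov modelling is planned, yet the text does not say that it supplies a comparator for this hypothesis.

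- **Wrong-direction reading of ratios.** For a cheaper, slightly less effective strategy a smaller cost-effectiveness ratio is the less favourable one, so a reader might fear misinterpretation. The article states no rule that would read it wrongly, and reporting rules for the ICER may sit in the full plan. I make no point of it.

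**Conclusion.** The point holds for the two hypotheses under Research questions and objectives. As worded they rest on ratios whose only randomised denominator is planned at zero, and they set equality without a margin. Under the planning assumption 95% of trials would give no bounded interval for either ratio. A true difference of 1 point leaves about 63% in that state without clustering, and about 79% if the variance is doubled.

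This rests on the randomised contrast with IADPSG being the denominator, on about 4,700 evaluable women per group, and on a 10% macrosomia rate. The article gives no planning rate for primary cesarean section, so the figures cover macrosomia only. The finding is that the two hypotheses are not reliably testable. It is not that they are untestable at any true difference, and it does not touch the QALY-based analysis.

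**What to change.** Under Research questions and objectives, replace the equal-NNT and equal-cost-of-prevention hypotheses with three statements on the difference scale:

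1. the risk difference in each primary outcome against its margin (the article gives 0.03 for macrosomia);
2. the cost difference versus IADPSG, with its interval;
3. incremental net benefit versus IADPSG, already planned, over a stated range of values per primary outcome avoided and per QALY, as the main economic estimate.

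Give NNT or cost per primary outcome prevented only where the interval for the effect difference excludes zero, and always beside the risk and cost differences themselves.

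The cost is the wording of two hypotheses, with no new data and no new analysis method. The downside is that there will be no single cost-per-case figure when the effects do not differ.

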### Overall study design

This is a randomized community-field trial including five GDM screening strategies in a parallel group design. Recruitment of the participants took place between September 2016 and January 2019 in 1015 health centers in 25 selected cities of five provinces of Iran.

All pregnant women < 14 weeks of gestation, who received prenatal care from governmental health care systems were eligible for enrollment, except where the following specific exclusion criteria prevented this: Maternal age < 18 years, preexisting diabetes, date of last menstrual period not certain, no ultrasound estimation from 6 to 14 weeks of gestational age available, chronic hypertension, asthma or currently receiving treatment with oral glucocorticoids, β-blockers, oral β-mimetics, Dilantin, or antiretroviral agents and past history of bariatric surgery.

All participants received standard prenatal care recommended by the American College of Obstetricians and Gynecologists (ACOG) [41]. Moreover, participants were scheduled to have two phases of GDM screening in the first and second trimesters of pregnancy, based on the pre-specified protocol for GDM screening, selected for each city.

At each prenatal visit, standardized questionnaires were administered to document prenatal as well as other data needed for research by trained midwives.

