### Randomization and allocation

Initially all provinces of Iran were categorized to five stratum based on their geographic location (North, East, West, South, and Center of Iran) and one province in each stratum were randomly selected; then, the list of the cities located in each province were provided. Since the socioeconomic status in the center of provinces may differ from other cities, in the second phase, all cities in each province were classified in two clusters of center of the province and other cities. At the end, four cities were randomly selected from the list of other cities in each province.

For allocation of protocols, in the cluster of the provincial centers, five different protocols were randomly allocated to each provincial center. Also, in the cluster of other cities, four other cities in each province were randomly allocated to the rest of the protocols (Fig. 1). Sample size for each city was estimated through probability proportional to size (PPS), defined by number of live births of the cities.

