### Data analysis

To illustrate distribution of the data, appropriate descriptive statistics such as measures of central tendency, index of dispersion and percentiles will be reported along with normality assumption testing through Kolmogorov-Smirnoff test. Maternal, neonatal and obstetric outcomes of the 4 less intensive screening strategies with IADPSG criteria will be compared using parametric or non-parametric statistical tests, where applicable.

In addition, based on the type of outcome variables, Generalized Linear Models (GLMs) with different link function such as linear, count or binary will be applied. Stepwise method with P-value < 0.2 will be used to identify significant confounding variables and estimate adjusted measures of interests. Moreover, longitudinal modeling through Generalized Estimating Equation (GEE) analysis approach will be conducted and to calculate Number Needed to Treat (NNT), the Linear GLM model will be applied as well. Since this is a cluster randomized trial, cluster effect in analysis will be considered.

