### Bayesian and Markov Modeling

Bayesian Cost Effectiveness Modeling (BCEM) will be used to overcome the complexity of the relationships linking a suitable measure of clinical benefit (e.g. quality-adjusted life years) and the associated costs. Simplifying assumptions, such as normality of the underlying distributions, are usually not granted, particularly for the cost variable, which is significantly skewed distributions. In addition, individual-level data sets are often characterized by the presence of structural zeros in the cost variable [65–67]. Bayesian models will be used to account for the presence of excess zeros in a distribution and have been applied in the context of cost data (Fig. 3).

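### The cost model adjusts for a minimization that the trial does not describe, and the economic models do not take up the trial's real allocation structure (25 cities, by province and provincial-centre status)

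*Protocol article*

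**What the plan says.** **Allocation (Randomization and allocation; Overall study design).** One province was drawn in each of five regions. Within each province the centre was handled apart from the other cities, because socioeconomic status may differ. For the centres, "five different protocols were randomly allocated to each provincial center". For the remainder, "four other cities in each province were randomly allocated to the rest of the protocols". I read this as one protocol per centre, with the other four protocols going to that province's other cities. Recruitment took place "in 1015 health centers in 25 selected cities of five provinces of Iran". Each protocol therefore has five cities, one per province, and exactly one of the five is a provincial centre. City samples were set in proportion to live births.

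**Cost model (Cost-effectiveness analysis).** Generalised linear models with a suitable variance function and link "will be used to identify the relationship between treatment allocation and costs after adjusting for minimization and the appropriate prognostic covariates at baseline". Recycled predictions then give the incremental effect. City, province and centre status are not mentioned.

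**Bayesian models (Bayesian and Markov Modeling).** These are justified by the link between cost and benefit, by skewed costs and by structural zeros: "Bayesian models will be used to account for the presence of excess zeros in a distribution". No city level is mentioned.

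**Clustering (last sentence of Data analysis).** "Since this is a cluster randomized trial, cluster effect in analysis will be considered". The sentence names no model, level or outcome.

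**The concern.** Comparing cost-effectiveness is the trial's stated aim. The paragraph that defines the cost comparison names one feature of the allocation to adjust for, minimization, and the allocation section describes no such procedure. It leaves out the three features that the allocation does have: city as the unit, province as a stratum, and centre versus other city as a second stratum.

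Two consequences follow if the models are fitted as written.

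- Women in the same city share whatever is local to prices, travel and hospital practice. A woman-level model without a city term counts them as independent, so intervals for cost, ICER and INB come out too narrow. The sensitivity, probabilistic and Markov analyses built on them inherit that.
- The provincial centre of each protocol lies in a different province. If centres contribute more women than other cities, pooling women without a province term weights the regions differently in each arm. A regional cost difference then appears as a difference between screening strategies.

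The results are meant to inform national screening policy, so both matter.

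**Working it through.** **Inputs from the protocol.** 25 cities, five per protocol; 5,200 women per protocol (Sample size calculation). The abstract gives a larger total: "This study is a randomized community non-inferiority trial among 30,000 pregnant women in five different geographic regions of Iran". That is 6,000 per protocol.

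**Input not in the protocol.** No ICC is given for cost or QALY. The sample size section uses a design effect of 0.001. A design effect is normally at least 1, so I read this value as an ICC. Larger ICCs below are assumptions.

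**The plan's own figure.** The step to 5,200 reproduces: 4,700 × 1.001 × 1.11 = 5,222. Clustering thus added 0.1% to the sample size, so the plan has no allowance there that would offset an omitted city term. (The 4,700 itself does not follow from its stated inputs, which give 2,610. That is a separate matter and does not affect this point.)

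**Design effect.** With equal cities, m = 5,200/5 = 1,040 women per city.

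- DE = 1 + (m − 1) × ICC = 1 + 1,039 × ICC
- Factor by which the standard error is too small = √DE
- Actual rejection rate of a nominal 5% two-sided test = 2 × [1 − Φ(1.96/√DE)]

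| ICC | DE | SE too small by | Coverage of nominal 95% interval | False rejection |
|---|---|---|---|---|
| 0.001 (plan's value, read as ICC) | 2.04 | 1.43 | 83% | 17% |
| 0.005 (assumed) | 6.20 | 2.49 | 57% | 43% |
| 0.01 (assumed) | 11.39 | 3.37 | 44% | 56% |
| 0.05 (assumed) | 52.95 | 7.28 | 21% | 79% |

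With 30,000 women, m = 1,200 and DE is 2.20 at an ICC of 0.001 and 12.99 at 0.01.

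Unequal cities raise these values. If one centre held half of an arm (2,600 women, and 650 in each of the other four cities; an assumption, as no city sizes are given), the weighted mean city size is (2,600² + 4 × 650²)/5,200 = 1,625. Then DE = 1 + 1,624 × 0.001 = 2.62 at an ICC of 0.001.

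These are normal approximations. They leave out the further loss from having only five cities per protocol.

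**Regional imbalance.** Under the same assumed split, protocol X draws 50% of its women from province p, where its centre lies, and 12.5% from each other province. Protocol Y does the same with province q. Pooled without a province term, the X − Y contrast contains (0.50 − 0.125) × (cost in p − cost in q), which is 0.375 of the regional cost difference. With equal city sizes this term is zero. Its size therefore depends on the actual proportional-to-births samples.

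**Degrees of freedom for a city-level check.** 25 cities − 1 − 4 (protocol) − 4 (province) = 16; adding centre status leaves 15. Each protocol and each province has exactly one centre, so the centre term can be estimated alongside the other two.

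**The case against.** The strongest reply is that the protocol has already dealt with this. The cluster sentence in Data analysis gives the design of the whole trial as its reason and is not confined to clinical outcomes. The cost paragraph fixes no standard-error method, resampling unit or interval, and recycled predictions yield a point contrast. The text is therefore compatible with cluster-robust errors or city random effects, and a condensed article may leave such detail to a fuller document.

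Much of this stands. A reader might infer that the plan has chosen to ignore clustering and that its ICER and INB results will be falsely certain. The protocol does not support that: it nowhere says that clustering will be ignored, and it contains a general commitment to the contrary. Nor does it name a probability of cost-effectiveness or an acceptability curve as an output; it mentions only a probabilistic approach. The larger error rates in the table rest on assumed ICCs, and nothing in the protocol shows that cost has a stronger city effect than other outcomes.

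What the reply does not answer is the minimization term. That is a stated adjustment for a procedure the allocation section does not contain, in the paragraph serving the trial's main aim. The general cluster sentence also supplies no province or centre term. GEE, which is named in the same section, is introduced there for longitudinal modelling, so it cannot be assumed to represent city.

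**Conclusion.** The point holds in conditional form. The cost-effectiveness section specifies an adjustment that does not match the allocation, and the economic models do not take up the general cluster commitment or the province and centre strata. If they are fitted as written, standard errors would be about 1.4 times too small at an ICC of 0.001, and about 3.4 times too small at an assumed ICC of 0.01. The first figure rests on reading the plan's 0.001 as an ICC and on equal cities of 1,040; unequal cities make it worse. A regional component in the protocol contrast is possible as well; its size cannot be fixed without the city sample sizes. If the analysts do apply the cluster commitment to cost and QALY, the understatement of uncertainty is removed. The minimization term and the missing strata would still need correction.

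**What to change.** In the cost-effectiveness section:

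- Delete the reference to minimization.
- State that the cost and QALY models include protocol, province and provincial-centre status as fixed effects and city as a random effect. City-level resampling with a small-sample correction would be an acceptable equivalent.
- Keep recycled predictions for the point estimate if wished, but take the uncertainty of ICER and INB from these models.

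In the Bayesian and Markov section, put the same city term in the Bayesian models and draw the probabilistic analysis from them.

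As a check, compute the mean INB of each city and analyse the 25 values with protocol, province and centre terms on a t distribution (15 residual degrees of freedom; 16 without the centre term).

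The cost is a change of wording and slightly more modelling. City, province and centre status are known from the allocation, so no new data or participants are needed. The downside is wider intervals.
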